## Abstract

**Background:**

Axial spondyloarthritis (AxSpA) produces structural changes that cause alterations in body functions. One tissue that seems to have a predictive role in the etiology and progression of the disease is the soft tissue, particularly the fascia. However, little is known about the use of myofascial induction in people with AxSpA, and clinical evidence from physiotherapy regarding potential strategies is limited.

**Objective:**

To evaluate the efficacy of myofascial induction compared with its simulation on joint amplitude in people with AxSpA.

**Methods:**

In this randomized controlled parallel superiority clinical trial, 84 people with an AxSpA diagnosis confirmed by a rheumatologist will be randomly assigned to groups: the experimental group or the control group. The experimental group will receive myofascial induction, and the control group will undergo a simulation of the technique. Both groups will receive an examination session and six intervention sessions twice per week for three weeks. A baseline follow-up will be performed immediately after the intervention and four weeks after treatment.

**Conclusion:**

The results of this study may contribute to a better understanding of the efficacy of myofascial induction for joint mobility in people with AxSpA. The implications of these results have a potential transformative effect on the understanding, analysis, evaluation, and physiotherapeutic treatment of this health condition.

**Trial registration:**

ClinicalTrials.gov NCT04424589. Registered 11 June 2020.

## Introduction

Axial spondyloarthritis (AxSpA) is a chronic and disabling disease that mainly affects young people and causes clear mobility and functional capacity limitations [1]. According to Londoño et al., in Colombia, its prevalence is 0.11% among the population over 18 years of age, with a 3:1 male–female ratio [2]. Although AxSpA is not among the most prevalent rheumatic conditions in the country, it is regarded as an inflammatory disease with higher rates of functional limitation and disability for affected people [3]. Swinnen [4] showed that a combination of personal factors such as depression, impotence due to disease progression, and coping capacity explained approximately 24% of the variation in activity limitations in AxSpA in contrast to biological factors, which represented only 10% of the variation [4].

Given the above information, the management of this condition requires solid interdisciplinary actions that meet the needs of individuals with AxSpA [3, 5]. Although pharmacological therapy is the basis of the treatment of this condition [6], nonpharmacological management is an indispensable complement, since it seeks to improve physical and psychological symptoms, readjust the circumstances of patients according to their conditions, and restore bodily movement [5, 7]. Different studies have shown that pharmacological therapy in conjunction with physical rehabilitation is more effective for managing severe symptoms, improving quality of life, fostering independence in activities of daily living, and optimizing anthropometric measurements related to the transverse muscle diameter and fat percentage than biological therapy, which has been demonstrated to not be equally effective when used alone [4, 5, 8–10].

Based on physiotherapy, various effective strategies have been developed for the management and control of AxSpA [11, 12]. However, orthopedic manual therapy (OMT) techniques focusing on soft tissue management have not been fully studied; therefore, their efficacy is uncertain in this population [13, 14]. Fascia, which is considered a predictor of joint mobility and axial structure and whose basal tone is not dependent on the central nervous system but on the innate resistance of its composition, appears to have a determining role in the etiology of this disease [15, 16].

Masi et al. stated that the increase in this tone at rest can predispose an individual to developing AxSpA [17], because a greater tension load in the fascia limits the transmission of forces from the enthesis to the spine, resulting in inflammatory changes and local mechanical stress [16, 18]. This anomalous tension causes alterations in the composition of the fascial tissue with an increase in myofibroblasts and a decrease in surrounding water, hyaluronic acid, and proteoglycans [17, 19]. These biochemical responses result in an increase in myofascial thickness and superposition of dehydrated collagen layers, triggering clinical pictures consistent with nonspecific and inflammatory pain, functional limitation, and loss of muscle elasticity among people with AxSpA [20, 21]. These signs become the therapeutic targets of myofascial induction, which is understood as a technique involving guided mechanical forces of low load and a long duration. Its effectiveness has been demonstrated in different mechanical and inflammatory pathologies, and its mechanism of action allows reorganization of fibroblasts and collagen layers, contributing to transformation of the fundamental substance from a densified state to a more fluid state, which results in clinically better patterns of movement in patients [10, 13, 22–24].

### Primary objective

The objective of this study will be to evaluate the efficacy of myofascial induction compared to its simulation on joint amplitude in people diagnosed with AxSpA.

### Secondary objective

The secondary objective will be to describe changes in the quality of life and functionality of people with AxSpA between the groups analyzed.

### Hypothesis

The myofascial induction group will have better results than the simulation group with respect to joint mobility among people with AxSpA.

### Study environment

This study will be conducted in an outpatient service center for people with rheumatic diseases in the city of Bogotá, Colombia.

### Inclusion criteria

People of both sexes over 18 years of age.People with a rheumatology-confirmed diagnosis of AxSpA regardless of the level of disease activity.People with the cognitive ability to follow orders.People who agree to participate in the study.

### Exclusion criteria

People receiving oral or parenteral coagulation therapy.Pregnant women.People with kinesiophobia.People with previous physical therapy in the last 15 days.The presence of active cancer or current treatment with chemo- or radiotherapy.

### Intervention

The study interventions are based on the myofascial induction techniques proposed by Andrezj Pilat [21]. The physiotherapist (PT) who performs this procedure in the experimental group will be trained and certified in this technique by the author in question. All techniques will be performed in all planned treatment sessions. 6 myofascial induction and simulation sessions will be done, two per week, every other day, for 3 weeks. Patients will be followed up one month after the last session with final evaluation.

### Experimental group intervention

#### J stroke

After a palpatory examination of the fascia, with the participant in prone position, the PT will apply slight superficial traction with his nondominant hand, which helps maintain tension on the myofascial tissue of the dorsolumbar spine. With his dominant hand, he will move his third finger up to the second level of the distal phalanx while the forearm is pronated, and then he will perform the “J” stroke, slowly sliding with nonpainful superficial depth, and rapid supination in the shape of a “J” on the site of the myofascial restriction. For each of the sites perceived as adhered or restricted, an average of seven J strokes should be performed. This technique does not require any lubricant or contact medium.

#### Release of the paravertebral fascia

The participant will be in a sitting position with the back uncovered, the contacts of the PT will be the knuckles of the second, third, and fourth fingers, the participant will be asked to flex the head, and the contacts will be moved up to the second thoracic vertebra. Once the movement is stopped, the therapist will bring back one of his lower extremities. At this point, he will continue the maneuver, keeping the elbows in extension and leaning on his body mechanics to gain depth. Then, he will ask the participant to slowly flex forward while keeping the legs in abduction while the PT slides the contacts caudally until reaching the high lumbar vertebrae. At each site where a movement restriction is perceived, he will stop without increasing the pressure for seven seconds. This process should be repeated three times.

#### Technique for releasing the quadratus lumborum

The participant will be in the lateral decubitus position with knee and hip flexion of 90°. The PT will remain bipedal in front of the patient at the height of the torso, the cranial hand will fix the ribs in an ascending direction, and the distal hand will be positioned with the ulnar edge of the hand in the space between the iliac crest and the last rib. The PT will seek to gain depth in this space until resistance is felt. Once he reaches the maximum allowed tissue barrier, he will perform a rhythmic, low-amplitude, flexion and extension movement of the elbow for 15 cycles in three repetitions.

In a following moment, in the same position, the patient will slightly drop the legs outside the table, the PT will accompany this tensioning of the quadratus lumborum, locating the pads of the fingers within the common paravertebral mass, and the PT will perform a slide his fingers in the transverse direction without generating flexion of the carpus. He will perform 13 cycles in three repetitions.

This technique will end with the patient in the lateral decubitus position, the legs will fall slightly outside the table, and the PT will have his hands crossed, with one on the iliac crest and another on the rib cage. He will begin by applying light traction on the skin, and then with light pressure, he will try to overcome the barriers of the tissue by facilitating movement of the fascia with sustained pressure for five minutes.

#### Release of the sacroiliac fascia

The patient will remain prone with knee flexion at 90°, the PT will remain bipedal next to the limb to be worked on, and the PT’s cranial hand will rest on the sacrum in the direction of the iliac crests while maintaining internal rotation of this limb with the caudal hand. He will maintain the pressure until it surpasses between three and six tissue barriers, which should be sustained for four minutes.

#### Sustained pressure technique in the upper trapezius

For the neck, the myofascial release technique will be used in the upper trapezius, the patient will be supine, and the PT will position his hands at the head of the table while seated as follows: His nondominant hand will support the patient. The dominant hand with 90° flexion will be at the level of the metacarpophalangeal joints, and the initial contact with the upper trapezius and angular muscles of the scapula will begin gently and progressively with the tips of the fingers, increasing the pressure and depth of the position of the hands. The PT will feel each of the tissue barriers and slowly yield to the pressure. This position will be maintained for five minutes.

#### Cross-hand technique in thoracolumbar fascia

The intervention continues with the cross-hand technique; at this time, the PT will be located on one side of the table, and the patient will have the back uncovered and be in the prone position. The PT will synchronize his breathing with that of the patient. Once he has taken two deep inhalations, the therapist will place the palms of his hands completely on the patient’s back at the level of the lumbosacral region with the fingers in slight abduction, and he will begin applying light traction on the skin, bringing the tissue to a state of pretension; slight pressure will be maintained for five minutes. Once the technique is complete, the pressure will be slowly released, and before removing the hands from the segment, manual contact will be maintained for 10 seconds. Once the hands are removed, the patient will be allowed to rest on the table for approximately two minutes to avoid vasovagal responses.

#### Control group intervention

The simulation intervention in the control group will suggest modification of basic parameters that does not alter the visual demonstration of the technique. The PT assigned to this group will omit the basic principles of myofascial induction: traction, sustained pressure, and tissue depth. All the proposed strategies for the experimental group will be carried out.

#### Discontinuation of participation

During the course of the study, any participant can choose to withdraw from the trial at any time. Participants can choose to suspend treatment and/or evaluations in the study but can remain in the follow-up if they wish; however, participants can also withdraw their consent, which implies that they wish to completely withdraw from the study, completely restricting the researchers’ access to the data obtained to date and those participants’ clinical histories.

### Outcomes

The primary outcome will be joint mobility measured by the Bath Ankylosing Spondylitis Metrology Index (BASMI). The secondary outcomes will be the Bath Ankylosing Spondylitis Functional Index (BASFI), Bath Ankylosing Spondylitis Disease Activity Index (BASDAI), and the Ankylosing Spondylitis Quality of Life Questionnaire (AsQol) [27, 28]. Each of these variables will be measured before the intervention, after the intervention, and four weeks after the intervention. The participants will undergo an initial evaluation before randomization. The results will be collected at each time point according to (Figs 1 and 2).

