### Sample size

The sample size was calculated in the program R Studio version 3.5.3, package of superiority clinical trials, based on a mean difference of 4.0 in the BASMI with a standard deviation of 2, an r (ratio) between groups of 1, and assuming a loss of 20%. An alpha one sided of 0.05% and a power of 0.80 were estimated based on mean difference test corresponding to a clinical trial of superiority (repeated measures ANOVA). The total number of people was 82 (42 per arm). Non probabilistic purposive sampling will be used.

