### Statistical analysis

The data will be analyzed in the latest version of the R Studio program. A statistical analysis will be performed based on the purposive analysis principles. The assumption of normality for the quantitative variables will be verified with the Shapiro–Wilk test, followed by a descriptive analysis; for the continuous variables, measures of central tendency or dispersion according to the data will be applied. For categorical variables, the proportions and frequencies will be calculated. Differences between the groups in measurements for the primary and secondary objectives will be analyzed by repeated measures ANOVA the variables with a normal distribution. Nonparametric tests will be performed if the data do not comply with the assumption of normality, interaction of arm by time effect will not be tested. Qualitative variables will be evaluated with the chi-square test of independence or Fisher’s exact test, as appropriate. For all tests, a significance level of p <0.05 will be employed.

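### No primary time point is fixed for BASMI, and the planned arm effect averages over visits, so neither an immediate nor a retained effect is tested

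*Protocol article*

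**What the plan says.** The Outcomes section of the protocol article makes BASMI primary and gives it, like the secondary scales, three time points: "Each of these variables will be measured before the intervention, after the intervention, and four weeks after the intervention". The Primary objective and Hypothesis sections attach no visit to the claim. The Intervention section describes the assessment one month after the last session as the final one, but does not call it primary.

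The Statistical analysis section says: "Differences between the groups in measurements for the primary and secondary objectives will be analyzed by repeated measures ANOVA", for normally distributed variables. It continues: "Nonparametric tests will be performed if the data do not comply with the assumption of normality", and the same sentence ends with "interaction of arm by time effect will not be tested". The level is common to everything: "For all tests, a significance level of p <0.05 will be employed". The section mentions no baseline covariate, no change score and no order of testing.

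The Sample size section uses one mean difference (4.0, SD 2), refers to repeated measures ANOVA, and names no visit.

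**The concern.** For a three-week course of manual therapy, an effect seen straight after the last session and an effect still present four weeks later are different claims. The plan collects data for both but does not say which one the trial is meant to establish.

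The model does not settle it. With arm and visit in the model and no interaction, the arm effect is the between-arm difference averaged over whichever visits are included. If baseline is among them, the average includes a visit at which randomisation makes the expected difference zero. A real effect is then understated, and a significant result cannot be read as an immediate or a retained benefit. If the normality check sends the analysis to the fallback, the text does not say which test is used or at which visit, so that choice could be made after the data are seen.

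**Working it through.** **1. What the sample size statement tells us.** It might have revealed the intended contrast, so I tried to reproduce it. With n per arm = 2(z₁₋α + z₁₋β)²σ²/δ², δ = 4.0, σ = 2 and power 0.80:

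- one-sided α = 0.05: 2 × (1.645 + 0.842)² × 4/16 = 3.1, so 4 per arm, and 4/0.8 = 5 after 20% loss;
- two-sided α = 0.05: 3.9, so again 4 and 5;
- one-sided 0.05% as printed (α = 0.0005): 8.5, so 9 per arm, and 9/0.8 = 11.25, so 12 after loss.

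None approaches the stated 42 per arm. That is a separate matter. Here it means only that the calculation does not identify a visit or a contrast.

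**2. What the averaged arm effect estimates.** Let d be the true difference at a visit where the treatment works. The expected difference at baseline is 0.

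| True pattern (baseline, post, 4 weeks) | Average with baseline | Average of the two post-treatment visits |
|---|---|---|
| 0, d, d (sustained) | (0 + d + d)/3 = 2d/3 | d |
| 0, d, 0 (immediate only) | d/3 | d/2 |
| 0, 0, d (late only) | d/3 | d/2 |

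On the plan's own difference of 4.0, the first column gives 4.0 × 2/3 = 2.67 for a sustained effect and 4.0/3 = 1.33 for a one-visit effect. Immediate-only and late-only effects give the same value, so the test cannot tell them apart.

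**3. Error rate of that test.** With complete data, the arm main effect is a two-sample t-test on each participant's mean over visits. Simulated under no effect (three visits, 42 per arm, 20,000 runs), it rejects in 5.3%, 5.2% and 5.1% of runs at correlations 0.5, 0.8 and 0.9. That is the nominal level apart from simulation error.

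**4. Error rate if visits were tested separately.** Suppose instead that arms were compared at each post-treatment visit at 5% and success on either counted. The rate is 1 − P(neither test rejects), from a bivariate normal with correlation ρ. The document gives no ρ, so the values are assumed.

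| ρ | Two-sided 5% | One-sided 5% |
|---|---|---|
| 0 | 1 − 0.95² = 9.75% | 9.75% |
| 0.5 | 9.1% | 8.8% |
| 0.8 | 7.8% | 7.5% |
| 0.9 | 7.0% | 6.8% |

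Mann–Whitney tests at either visit (42 per arm, 4,000 runs) simulate at 9.2%, 8.2% and 7.1% for ρ = 0.5, 0.8 and 0.9.

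**5. Power of the alternative.** Assume equal correlations ρ between all visits, equal variances σ² and a sustained effect d. The signal-to-noise ratio, in units of d/σ and leaving out the common factor for group size, is:

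- average including baseline: (2/3)/√((1 + 2ρ)/3);
- baseline-adjusted difference at one visit: 1/√(1 − ρ²).

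At ρ = 0.5 these are 0.667/0.816 = 0.82 and 1/0.866 = 1.15. At ρ = 0.8 they are 0.667/0.931 = 0.72 and 1/0.6 = 1.67. The adjusted contrast is stronger at both. Against an average of the two post-treatment visits only, 1/√((1 + ρ)/2), the values are 1.15 at ρ = 0.5 (equal) and 1.05 at ρ = 0.8 (the adjusted contrast is again stronger).

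**The case against.** The strongest reply is that the plan specifies a single test. A repeated measures ANOVA without an interaction gives one arm effect, and one mean difference in the sample size fits that. A reader might infer from two post-treatment visits and a blanket 5% level that success may be claimed on either visit and that the primary error rate exceeds 5%. The document does not support this: it plans no visit-by-visit comparison and states no either-visit rule, and step 3 shows the planned test at its nominal level. This part of the reply stands in full.

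Nor does the fallback have to compare arms visit by visit. A rank test on a change score or on the post-treatment mean, or a rank-based repeated measures method, would give one comparison. The choice of test may also sit in an analysis plan that is not shown. This stands too: the text leaves separate testing open but does not require it.

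Two points remain. First, the article does address outcome timing and the primary model, and the combination it fixes targets no identifiable clinical effect. That is a fault in what is stated, not an omitted detail. Second, the clause on the interaction is attached to the fallback sentence, so its scope is not entirely clear. If it applies only to the fallback, the ANOVA's primary term is not identified at all.

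**Conclusion.** The point holds as a defect in the definition of the primary comparison, not as a demonstrated inflation of error. The planned arm effect holds about 5%. It estimates 2/3 of a sustained effect or 1/3 of a one-visit effect if baseline is a repeated measure, which is an assumption because the text does not list the visits in the model. Without baseline, a sustained effect is not diluted and a one-visit effect is halved, but immediate and retained effects still cannot be told apart.

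The 7–9% figure is conditional on three things the document does not state: separate tests at both post-treatment visits, success on either, and correlations of 0.5–0.9. It measures the room left by the unspecified fallback and should not be quoted as the trial's error rate. The timeline and flow figures were not available to me; the caption of the first describes a schedule of measurements, not a primary visit.

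**What to change.** Name one primary contrast: the baseline-adjusted BASMI difference between arms at one prespecified post-treatment visit. The sponsor chooses the visit according to whether an immediate or a retained effect is the main claim. Estimate it by ANCOVA, or by a repeated measures model of the post-treatment visits with arm-by-visit terms and baseline as covariate. Test the other visit only if the first is significant, each at the full level (fixed sequence). Apply the same visit and order to any nonparametric fallback, and tie the sample size statement to this contrast.

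The cost is a changed primary model and a few sentences in Outcomes, Sample size and Statistical analysis, with no new data. For a sustained effect at equal correlations of 0.5–0.8, the contrast has more power than an arm effect averaged over all three visits. The price is that an effect absent at the chosen visit will not be found there, so the choice must be made before the data are seen.

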**Fig 1 pone.0286885.g001:**
[figure not shown]
Standard Protocol Items: Recommendations for Interventional Trials (SPIRIT) timeline of measurements. Time represented by weeks (WK).

